### 10.3.3 Special cases

#### ADVERSE EVENT OF SPECIAL INTEREST

An adverse event of special interest (AESI) is a serious or non-serious adverse event that requires special attention and will be specifically searched. AESIs should be notified and followed as serious adverse events.

There is no AESI as part of this research.

#### REPORTING EXCEPTIONS

##### Serious adverse event not to be notified immediately

Any event that is part of the natural history of the disease (progression of the disease or hospitalization for progression of the disease) should not be notified to pharmacovigilance on the SAE form but has to be reported into the e-CRF.

Some "hospitalization/prolongation of hospitalization" are not considered as serious adverse events and do not require notification to pharmacovigilance (see last paragraph "Serious adverse event").

#### PREGNANCY

If a woman starts a pregnancy as part of the study or in some cases if her partner participates in the study (drug that can reach the seminal line of the man), the investigator has to report pregnancy to the sponsor.

The investigator informs the sponsor who will send him a "pregnancy notification form". This form must contain the expected date of delivery, the contact information of the obstetrician and the maternity ward provided for delivery if the pregnancy continues.

The investigator has to follow the patient until the end of the pregnancy or its interruption and notify the outcome to the sponsor. If the outcome of pregnancy falls within the definition of serious adverse events (spontaneous abortion with hospitalization, fetal death, congenital anomaly, ...) the investigator should follow the SAE reporting process.

If it is a paternal exposure, the investigator has to obtain the parturient consent to report pregnancy data.

## 11 STATISTICAL CONSIDERATIONS

### 11.1 SAMPLE SIZE

The primary endpoint is the proportion of patients for whom the first-line imaging technique (MIBI SPECT/CT or FCH PET/CT) allows guiding the surgical procedure appropriately, i.e. -say to decide on a true positive minimally invasive surgery and to obtain the patient's cure one month post-operatively.

Considering that the proportion of patients guided towards the right surgical strategy according to first-line imaging is 60% with MIBI SPECT/CT [Cheung, 2012] and 90% with FCH PET/CT [Quak, 2017], 50 evaluable patients (25 per arm) are necessary to detect such a difference in proportions with a risk of 5% and a power of 80% (one-sided test). It is planned to include 58 patients to anticipate 15% of possible non-evaluable patients. Based on the results of our published APACH-1 study [Quak, 2017] where a sensitivity of approximately 90% was observed with FCH PET/CT, we believe that a unilateral test is sufficient in the design of the design of APACH-2 to demonstrate the superiority of FCH PET/CT compared to MIBI SPECT/CT which has a sensitivity of approximately 60%.

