|                              | 
a discrepancy, the examinations will be reviewed in a Multidisciplinary Consultation Meeting (RCP), and the result of the review of the examination will be communicated to the surgeon.
 
Surgical decision for each diagnostic strategy
 
In case of positive results of the first and/or second exam, the surgery will consist of a minimally invasive procedure under extemporaneous, on an outpatient basis.
 
In case of negative imaging results (MIBI and FCH), an exploration of the 4 parathyroid sites will be performed.
 
In the case of multiple or ectopic PTAs, the surgical procedure will be adapted.
 
Histopathological examination of the surgical specimens will confirm the presence or absence of PTA.
 
The results of the imaging assessment will be compared with the surgical and pathological results.
 
Patients will be seen 1 and 6 months post-surgery with a blood test to assess normalization of serum calcium and PTH.
 |
| Sample size           | 
Considering that the proportion of patients referred to the right surgical strategy according to first-line imaging is 60% with MIBI SPECT/CT [Cheung, 2012] and 90% with FCH PET-CT [Quak, 2017], 50 evaluable patients (25 per arm) are needed to detect such a difference in proportions with a risk of 5% and a power of 80% (unilateral test). It is planned to include 58 patients to anticipate 15% of possible non-evaluable patients.
                                                                                                                                                                                                                                                                                                                                                                                                                                                                                                                                                               |

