## 4 SCIENTIFIC RATIONALE OF THE STUDY

### 4.1 BACKGROUND

Primary hyperparathyroidism is a common endocrine disease, related to autonomic overproduction of parathyroid hormone (PTH), usually by a parathyroid adenoma (PTA). The diagnosis is confirmed by a laboratory test. Excision of PTA remains the only curative treatment: despite a diagnosis often at an asymptomatic stage, normalization of hypercalcemia by excision of PTA improves bone mineral density and quality of life of patients. Bilateral cervical exploration of the parathyroids is now supplanted by minimally invasive surgery requiring precise localization of the PTA preoperatively. This minimally invasive technique, usually performed on an outpatient basis under local anesthesia, is associated with a better cure rate and fewer complications than bilateral cervical exploration, and at a lower cost (Udelsman-2011).

The current diagnosis to localize PTA is based on Tc99m-sestaMIBI (MIBI) scintigraphy with tomographic acquisition and CT scanning, negative in 33% of cases, leading to the proposal of bilateral cervical exploration (Ciappuccini-2012).

The recent literature and the results of our prospective APACH1 study (NCT02432599) strongly suggest the best diagnostic value of positron emission tomography coupled with F18-choline (FCH) CT scanning. Out of 25 patients with primary hyperparathyroidism and a negative MIBI scan, second-line FCH PET/CT was positive in 19 patients guiding parathyroidectomy and successfully reduced operative time in the majority of patients (Quak-2017).

Although FCH PET/CT is not yet used as a first-line treatment for primary hyperparathyroidism (cost of examination, availability of PET cameras, lack of marketing authorization for FCH in this indication), its contribution to guiding the surgical procedure seems promising. It therefore seems interesting to question the place of FCH PET-CT as a first-line imaging technique to localize PTA in biologically confirmed primary hyperparathyroidism, while taking into account the costs.

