## 11.2 STATISTICAL ANALYSIS

For the main objective, the proportions of patients oriented towards the right surgical strategy (decision for true positive minimally invasive surgery and obtaining the patient's cure) according to first-line imaging (MIBI SPECT/CT or FCH PET/CT) will be compared using a chi2 test with a one-sided alpha risk of 5%.

Qualitative variables will be described using numbers and percentages; Quantitative variables will be described using mean and standard deviation or quartiles as appropriate. Estimates will be provided with their bilateral 90% confidence intervals. We will calculate Cohen's kappa coefficients (with their 95% confidence interval) which will be considered strong if greater than 0.60, quasiperfect if greater than 0.80, perfect if equal to 1, and unsatisfactory otherwise.

The performance (sensitivity, specificity, error rate, positive and negative likelihood ratios) of the two interventions (FCH PET/CT and MIBI SPECT/CT) will be assessed using univariate analyses, Chi test or Fisher's exact nonparametric test.

It is also planned to use multivariate logistic regression models to identify possible other parameters associated with the correct surgical strategy.

For patients who received both imaging techniques sequentially, we will describe their socio-demographic and clinical characteristics, as well as the proportion of minimally invasive surgeries and bilateral explorations. Depending on the number of patients, non-parametric comparisons will be made.

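### Section 11.1 plans on 60% and 90% as rates of the composite endpoint, but the same paragraph gives them as scan sensitivities, with no cure rate to link the two

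*Protocol*

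**What the plan says.** Section 11.1 opens by defining the primary endpoint as a composite: the first-line scan leads to a true-positive decision for minimally invasive surgery, and the patient is cured one month after the operation. It then assumes that "the proportion of patients guided towards the right surgical strategy according to first-line imaging is 60% with MIBI SPECT/CT" "and 90% with FCH PET/CT", with the 90% credited to the earlier APACH-1 study. The synopsis uses the same rates and concludes that "50 evaluable patients (25 per arm) are needed to detect such a difference in proportions with a risk of 5% and a power of 80" per cent. Section 11.2 says the two proportions "will be compared using a chi2 test with a one-sided alpha risk of 5" per cent.

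Two sentences after stating the planning rates, section 11.1 defends the one-sided test by citing APACH-1, "where a sensitivity of approximately 90% was observed with FCH PET/CT", and by giving MIBI SPECT/CT a sensitivity of about 60%.

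Cure is defined in two ways. Section 6.1 asks for normal serum calcium at one month. The main criterion in the synopsis asks for normal calcium and PTH at both one and six months. No section gives an expected cure rate.

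**The concern.** Sensitivity describes a scan. The endpoint describes a patient who was scanned, operated on by the minimally invasive route because of that scan, and then cured. A sensitivity contains no cure component, so it can equal the composite rate only if nothing is lost between a true-positive scan and cure. The paragraph uses one pair of numbers for both quantities and offers no conversion.

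The trial's size and its claim of 80% power rest on this pair alone. If the true composite rates are lower in both arms, the absolute difference shrinks and the rates move towards 50%, where the variance is larger. Both effects reduce power. A non-significant result would then be read against a power that the trial may not have had.

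**Working it through.** **Inputs.** From section 11.1: 60% and 90%, one-sided 5%, 80% power, 25 evaluable per arm. From section 11.2: a one-sided chi-square test. I take the test without continuity correction, since that form reproduces 25 per arm. Not in the protocol: the share of true-positive scans that end in minimally invasive surgery and cure. I call this the cure rate, c, for short. It is **assumed**, equal in both arms, and shown from 80% to 100%.

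**Step 1: reproduce the plan.** With pooled variance under the null,

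n per arm = [1.645·√(2·p̄·(1−p̄)) + 0.842·√(p1(1−p1) + p2(1−p2))]² / (p2−p1)²

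At p1 = 0.60, p2 = 0.90, p̄ = 0.75: [1.645·√0.375 + 0.842·√0.33]² / 0.09 = 24.7, so 25 per arm. The plan's figure reproduces. Power at 25 per arm is 80.4% by the normal approximation and 82.1% by exact binomial enumeration of the chi-square test.

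**Step 2: treat the figures as sensitivities.** All patients have laboratory-confirmed disease, and surgery follows the scan result. The composite rate in each arm is then approximately sensitivity × c.

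Worked line for c = 0.95: p1 = 0.60 × 0.95 = 0.570, p2 = 0.90 × 0.95 = 0.855, difference 0.285, p̄ = 0.7125. Approximate power = Φ[(0.285·√25 − 1.645·√(2·0.7125·0.2875)) / √(0.570·0.430 + 0.855·0.145)] = Φ[(1.425 − 1.053)/0.608] = Φ(0.61) = 73%. The exact value is 73.8%.

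| Assumed c | MIBI vs FCH composite | Approx. power, 25 per arm | Exact power, 25 per arm | n per arm for 80% |
|---|---|---|---|---|
| 100% | 60.0% vs 90.0% | 80.4% | 82.1% | 25 |
| 98% | 58.8% vs 88.2% | 77.4% | 78.7% | 27 |
| 95% | 57.0% vs 85.5% | 73.0% | 73.8% | 31 |
| 90% | 54.0% vs 81.0% | 65.9% | 66.9% | 37 |
| 85% | 51.0% vs 76.5% | 59.5% | 61.3% | 43 |
| 80% | 48.0% vs 72.0% | 53.6% | 56.4% | 51 |

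(The last column uses the formula in step 1.)

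**Step 3: the non-evaluable allowance.** If all 58 included patients were evaluable (29 per arm), approximate power would be 78.6% at c = 95% and 71.7% at c = 90%. The allowance does not close the gap.

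**The case against.** The best defence is that the protocol does label 60% and 90% as endpoint rates. Section 11.1 and the synopsis call them proportions guided to the right surgery, and section 11.2 explains that phrase as the composite, cure included. The sensitivity sentence comes later and has another job, which is to justify a one-sided test. The cited studies may report composite rates as well; that cannot be checked here, and the source given for the 60% is absent from the reference list. This stands as far as it goes: one cannot assert that the figures are sensitivities and nothing else. What remains is that one paragraph gives the same numbers as two different quantities and does not connect them.

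It is also fair that the gap is mainly cure. In patients who all have the disease, a patient-level sensitivity already counts true-positive scans, and section 7.4.4 makes minimally invasive surgery the rule after a positive scan, apart from multiple or ectopic adenomas.

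Three stronger readings are tempting, and the documents do not support them.

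- A reader might take from section 4.1, where "second-line FCH PET/CT was positive in 19 patients guiding parathyroidectomy" out of 25, that the FCH rate is really 76%. Those patients all had a negative MIBI scan. The figure is second-line and does not estimate first-line performance.
- A reader might combine that 76% with MIBI being "negative in 33% of cases, leading to the proposal of bilateral cervical exploration" to get 0.67 + 0.33 × 0.76 = 92% as a ceiling on FCH positivity. The exact 95% interval for 19 of 25 is 55% to 91%, which carries through to about 85% to 97%. So 92% is not a ceiling, and it does not contradict a 90% planning rate.
- A reader might lower only the FCH rate and hold MIBI at 60%, which gives a much larger loss of power. Non-cure would affect both arms, and the protocol gives no ground for treating its two figures differently.

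**Conclusion.** The point holds as a fault in a planning assumption. It is not an arithmetic error, since 25 per arm follows from 60% versus 90%. The stated 80% power is unsupported for the composite endpoint, because the protocol equates sensitivity with that endpoint and gives no cure rate.

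The size is conditional. If the two figures are sensitivities and one assumed cure rate applies in both arms, exact power at 25 per arm is about 79%, 74%, 67% and 56% for cure rates of 98%, 95%, 90% and 80%. If they are already composite rates, nothing is lost and only the wording is at fault. The link to sensitivity is firmer for the 90%, where number and source both match, than for the 60%, where only the number matches. The stricter cure definition in the synopsis can only lower the composite relative to section 6.1.

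The type I error, the test and the planned estimates are unaffected. The point is worth correcting because the power statement is what a null result would be read against, but it does not invalidate the design.

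**What to change.** In section 11.1 and in the sample-size row of the synopsis:

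1. State whether 60% and 90% are sensitivities or composite rates. Give the source of each, and add the missing MIBI source to the reference list.
2. If they are sensitivities, derive the expected composite rate in each arm as the rate of true-positive decisions for minimally invasive surgery × cure. Do this under a single definition of cure, after section 6.1 and the synopsis have been reconciled.
3. Restate the power as a range, with the cure rate labelled as assumed. For example: 25 evaluable patients per arm give about 82% power if every true positive is operated on by the minimally invasive route and cured, and about 79%, 74% or 67% if the assumed cure rate in both arms is 98%, 95% or 90%.
4. Keep the sentence on sensitivity, since it is the stated reason for the one-sided test, but make clear that it describes scans and not the endpoint.

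The sample size and the analysis stay as they are. The cost is a wording change and, if the figures prove to be sensitivities, a less favourable stated power.

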## 11.2 STATISTICAL ANALYSIS

For the main objective, the proportions of patients oriented towards the right surgical strategy (decision for true positive minimally invasive surgery and obtaining the patient's cure) according to first-line imaging (MIBI SPECT/CT or FCH PET/CT) will be compared using a chi2 test with a one-sided alpha risk of 5%.

Qualitative variables will be described using numbers and percentages; Quantitative variables will be described using mean and standard deviation or quartiles as appropriate. Estimates will be provided with their bilateral 90% confidence intervals. We will calculate Cohen's kappa coefficients (with their 95% confidence interval) which will be considered strong if greater than 0.60, quasiperfect if greater than 0.80, perfect if equal to 1, and unsatisfactory otherwise.

The performance (sensitivity, specificity, error rate, positive and negative likelihood ratios) of the two interventions (FCH PET/CT and MIBI SPECT/CT) will be assessed using univariate analyses, Chi test or Fisher's exact nonparametric test.

It is also planned to use multivariate logistic regression models to identify possible other parameters associated with the correct surgical strategy.

For patients who received both imaging techniques sequentially, we will describe their socio-demographic and clinical characteristics, as well as the proportion of minimally invasive surgeries and bilateral explorations. Depending on the number of patients, non-parametric comparisons will be made.

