## 6.2 SECONDARY ENDPOINTS

The secondary endpoints are:

- Average cost of caring for a patient for each of the two strategies
- Sensitivity, specificity, error rates, positive and negative likelihood ratios of FCH PET/CT and MIBI SPECT/CT
- Rate of minimally invasive surgeries and bilateral cervical explorations for each diagnostic strategy
- Number of failures of parathyroid surgery (regardless of the type of surgery performed), defined by the persistence of primary hyperparathyroidism 6 months after surgery
- Complications occurring within one month of surgery: infections, hematomas, laryngeal recurrent nerve injury
- Cohen's kappa coefficients between the 2 independent readers, during their first reading, then during their second reading (3 months later); as well as between the first and second reading of each of the 2 readers
- Serum PTH concentration at baseline
- To compare detection sensitivities of FCH PET-CT at 10 min and 60 min post-injection, as well as semi-quantitative analysis.
- Scores for the 6 dimensions (comfort, attention, information, pain management, waiting times, intimacy) of the EVAN-G questionnaire administered perioperatively (4 to 48 hours after the intervention before discharge from hospitalization)

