### 7.3 SUBJECTS SELECTION

#### 7.3.1 Inclusion criteria

- Patient over 18 years of age
- Patient with primary hyperparathyroidism and for whom excision surgery is planned
- Laboratory assessment confirming the diagnosis of primary hyperparathyroidism (elevated serum PTH and calcium concentrations)
- For women of childbearing potential, negative pregnancy test at baseline
- Affiliation to a social security scheme
- Patient who has signed written consent

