#### ❖ **Surgical decision for each diagnostic strategy**

In case of positive results of the first and/or second exam, the surgery will consist of a minimally invasive procedure, on an outpatient basis.

In case of negative imaging results (MIBI and FCH), an exploration of the 4 parathyroid sites will be performed.

In the case of multiple or ectopic PTAs, the surgical procedure will be adapted.

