#### ❖ **Histopathological examination of surgical specimens**

Histopathological examination of the surgical specimens will confirm the presence or absence of PTA.

The results of the imaging assessment will be compared with the surgical and pathological results.

Patients will be seen again between 1 and 6 months post-surgery with a blood test to assess normalization of serum calcium.

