### **7.4.6 Dosimetry**

The radiation reduction strategy is specified below during each of the two imaging examinations under study. Only patients for whom the first-line examination is negative or non-contributory will perform the 2 imaging examinations.

For FCH PET, the injected activity will be reduced from 3.5 MBq/Kg (standard dose for a FCH PET examination in oncology) to 1.5 MBq/kg, or approximately 105 MBq for a 70 kg patient. In return, the acquisition time will be increased to 5 minutes per step in list mode. According to the FCH dosimetry literature, the effective dose received is 0.018 mSv per MBq injected (Giussani, JNM 2012; ICRP, 2013). The irradiation associated with the injection of FCH in our study is therefore estimated at 1.89 mSv.

For the MIBI examination, the injected dose for the SPECT examination is 750 MBq of Sestamibi labelled with 99mTc. The effective dose received is 0.009mSv/MBq (see MA). The irradiation related to the injection for the SPECT is therefore 6.75mSv.

Each examination will be focused on the neck and upper mediastinum and the lenses will be excluded from the volume, in order to limit X-ray exposure. The dose-length product of a consecutive series of 31 patients of variable morphotype (body mass index range 15.4 to 38.1,

median 25.1) who underwent ENT-centered PET-CT in our PET unit was  $150.6 \pm 3.54$  mGy.cm, the expected CT dosimetry will be  $0.89 \pm 0.02$  mSv.

For the SPECT/CT, the dose received during the CT is about 50% more due to a 2-slice system instead of 64 on the CT of the PET. The dose received during the CT scan of the gamma camera is then of the order of 1.33mSv. The total effective dose of the two CT scans is in the order of 2.23mSv.

The total cumulative effective dose is therefore estimated to be 10.87 mSv.

**Radiation protection measures for patients** : As a precautionary measure, it is recommended that patients stay away from pregnant women and young children for an extended period of time for 12 hours after injection.

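### Specificity and likelihood ratios are planned in a cohort where every patient has the disease, and the FCH versus MIBI performance comparison is not limited to first-line scans

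*Protocol*

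**What the plan says.** Protocol section 6.2 lists as a secondary endpoint "Sensitivity, specificity, error rates, positive and negative likelihood ratios of FCH PET/CT and MIBI SPECT/CT". Section 11.2 carries it into the analysis: "The performance (sensitivity, specificity, error rate, positive and negative likelihood ratios) of the two interventions (FCH PET/CT and MIBI SPECT/CT) will be assessed", by chi-square or Fisher's exact test. Neither section names a unit of analysis (patient, side or gland) or says which scans count. The matching objective in section 5.2 is framed by strategy, not by technique.

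**Who is enrolled.** Section 7.3.1 requires "Patient with primary hyperparathyroidism and for whom excision surgery is planned" and "Laboratory assessment confirming the diagnosis of primary hyperparathyroidism (elevated serum PTH and calcium concentrations".

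**How the scans are verified.** Under section 7.4.4, "Histopathological examination of the surgical specimens will confirm the presence or absence of PTA", and imaging is set against the surgical and pathological findings. How much is explored depends on the scans: "In case of positive results of the first and/or second exam, the surgery will consist of a minimally invasive procedure", whereas "In case of negative imaging results (MIBI and FCH), an exploration of the 4 parathyroid sites will be performed". For multiple or ectopic adenomas the procedure is adapted.

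**Who is scanned twice.** Section 7.4.6: "Only patients for whom the first-line examination is negative or non-contributory will perform the 2 imaging examinations". Section 11.2 gives these patients a separate descriptive paragraph, with non-parametric comparisons if numbers allow. It does not say whether their second scans enter the performance comparison. The primary analysis in the same section is tied to first-line imaging.

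**The concern.** Specificity needs people without the target condition, and both likelihood ratios are built from specificity. The inclusion criteria remove such people at patient level. Moving to sites or glands restores a denominator, but then the reference standard is applied more or less fully according to the test result, which is partial verification.

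Separately, the performance comparison loses the first-line restriction that protects the primary analysis. If second-line scans were counted, part of each group would be patients selected for a negative or non-contributory first scan. The same people would also sit on both sides of a test that assumes independent groups. The comparison would no longer be the randomised one.

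At stake is a named secondary objective. A reader could be given accuracy indices that rest on almost nobody, or a between-technique p-value that does not compare like with like.

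**Working it through.** **1. The plan's own figure.** Section 11.1 assumes 60% (MIBI) and 90% (FCH), one-sided 5%, power 80%. With pooled variance and no continuity correction:

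n = [1.645 × √(2 × 0.75 × 0.25) + 0.842 × √(0.6 × 0.4 + 0.9 × 0.1)]² / 0.30² ≈ 24.7, so 25 per arm (power 80.4%).

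The stated 50 evaluable patients are reproduced. This supplies only the arm size used below; the protocol gives no figure for the performance analysis.

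**2. Patient-level specificity.** The share of operated patients without PTA on histology is not in the protocol. I assume 0-15%. Expected number per arm = 25 × share; chance of none = (1 − share)^25.

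| Share without PTA | Expected in an arm of 25 | Chance that the arm has none |
|---|---|---|
| 0% | 0 | 100% |
| 2% | 0.5 | 60% |
| 5% | 1.25 | 28% |
| 10% | 2.5 | 7% |
| 15% | 3.75 | 2% |

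With none, specificity is 0/0. If all n such patients are correctly negative, the lower limit of the exact 90% interval (the level set in section 11.2) is 0.05^(1/n): 5% for n = 1, 37% for n = 3, 47% for n = 4.

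The likelihood ratios inherit this. Take sensitivity as 90% and specificity between 0.37 and 1:
- LR+ = 0.90/(1 − specificity) runs from 0.90/0.63 ≈ 1.4 to infinity.
- LR− = 0.10/specificity runs from 0.10/0.37 ≈ 0.27 down to 0.10.

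**3. Site-level specificity.** Assume three unaffected sites per patient: 3 × 25 = 75 per arm. If 72 of 75 are correctly negative, the naive 90% interval is 90-99%. That precision is not real: it ignores clustering within patients and counts sites that nobody explored.

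As an illustration of how few patients would have all four sites explored, take 24% of second-line FCH scans as negative (19 of 25 were positive, section 4.1), MIBI negativity of 33% (section 4.1) to 40% (1 − 0.60), and second-line MIBI positivity of 0-60% (assumed):
- MIBI-first arm: 25 × 0.33 × 0.24 ≈ 2.0 to 25 × 0.40 × 0.24 = 2.4.
- FCH-first arm: 25 × 0.10 × 0.40 = 1.0 to 25 × 0.10 × 1 = 2.5.
- Total: about 3 to 5 of 50.

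**4. Second-line scans under a per-technique reading.** The planning rates are treated here as scan-positive rates.
- FCH: 25 × 0.33 = 8.25 to 25 × 0.40 = 10 second-line scans, out of 33.25 to 35. Share 25-29%.
- MIBI: 25 × 0.10 = 2.5 second-line scans, out of 27.5. Share 9%.
- Patients in both groups: 8.25 + 2.5 ≈ 11 to 10 + 2.5 ≈ 13 of 50.

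These counts are approximate. The 60% and 90% are rates of correct surgical guidance including cure. A patient with a false-positive scan, or one not cured, fails that endpoint without triggering a second scan.

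**5. Would counting second-line scans shift FCH sensitivity?** If second-line sensitivity were 76%: (25 × 0.90 + 10 × 0.76)/35 = 86%. If it were 90%: (25 × 0.90 + 10 × 0.90)/35 = 90%, no shift. The 76% is a positivity rate. Section 11.1 gives a sensitivity of about 90% for that same earlier study, whose patients had negative or inconclusive MIBI. The protocol therefore yields no size for this bias.

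**The case against.** The strongest reply is that the text fixes less than the concern needs. It never says the unit is the patient. Readers record the location of each focus, and histology is reported as presence or absence, so side- or site-level specificity is possible. Calcium and PTH at 1 and 6 months could act as an indirect reference for sites left unexplored. Unit, reference and analysis set are normal content for a statistical analysis plan, which is not at hand here.

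Much of this stands. A reader might infer that specificity cannot be estimated at all. The documents do not support that: histology may show no PTA in a few patients, and a site-level version can be defined.

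A reader might also infer that the plan pools all FCH and all MIBI scans. Section 11.2 does not say so. The objective is worded by strategy, patients scanned twice are handled in their own paragraph, and a first-line comparison by arm fits the text.

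Two things do not fall away. No later document can supply disease-free patients or verify unexplored sites directly, and the protocol does not name cure as the reference for this endpoint. And sections 6.2 and 11.2 do drop the first-line restriction, so the text permits a per-technique reading even though it does not order one.

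**Conclusion.** The point holds in a limited form.

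- Patient-level specificity and both likelihood ratios would be undefined or nearly uninformative: 0 to about 4 negatives per arm of 25, if 0-15% of patients have no PTA. That range is an assumption, but the conclusion does not change anywhere within it.
- Site-level specificity has a denominator but depends on a reference standard applied according to the scan result.
- The performance comparison is not limited to first-line scans. If second-line scans were counted, about a quarter or slightly more of the FCH scans and a tenth or less of the MIBI scans would come from selected patients, and some 11-13 of 50 patients would be in both groups.

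It would be tempting to add that FCH sensitivity would be pulled from 90% to 86%. That should not be claimed, because it substitutes a positivity rate for a sensitivity.

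This concerns a secondary endpoint. The primary comparison uses first-line imaging by randomised arm and is untouched.

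**What to change.** In sections 6.2 and 11.2:

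- Delete patient-level specificity and the positive and negative likelihood ratios.
- Compare sensitivity, and positive predictive value if wanted, on first-line scans only, by randomised arm, with confidence intervals.
- Report second-line yield separately, as conditional on a negative or non-contributory first scan, without a between-technique test.
- If site-level specificity is kept, report it descriptively, stating the unit and the reference used for unexplored sites.

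The cost is wording in two sections and fewer accuracy indices in the report. Sample size, imaging and surgical procedures do not change.
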